**Introduction**

Chronic low back pain (CLBP), a symptom rather than a disease, is commonly located between the lower rib and the buttocks wrinkles.(Hartvigsen et al., 2018) Similar to other symptoms, CLBP results from variable factors, and the specific underlying cause can be rarely identified.(Maher, Underwood, & Buchbinder, 2017) People of all ages may suffer from CLBP, it is uncommon in the first decade of life; however, the prevalence increases steadily during adolescence and peaks in midlife.(Hartvigsen et al., 2018) The lifetime morbidity of CLBP worldwide is up to 84%.(Bernstein, Malik, Carville, & Ward, 2017) CLBP was once seen as a short-term condition but is now considered as a long-term condition because of its frequent recurrent episodes. Approximately 33% of people experience relapse within 1 year after recovery.(Bernstein et al., 2017; Hartvigsen et al., 2018) Given its high prevalence and chronicity, CLBP is the leading cause of disability across the world, causing more disabilities than any other chronic diseases do.(Chou et al., 2017; Hartvigsen et al., 2018; National Guideline, 2016) From 2013 to 2016, CLBP consistently remained the top six most costly global health issues.(G. B. o. D. S. Collaborators., 2015; GBD 2015 Disease and Injury Incidence and Prevalence Collaborators., 2016; GBD 2016 Disease and Injury Incidence and Prevalence Collaborators., 2017) Consultation about back pain accounts for 7% of all general practitioner consultations,(Bernstein et al., 2017) and people with CLBP miss 4.1 million working days in 1 year.(Qaseem et al., 2017) Undoubtedly, low back pain is now a substantial public health challenge worldwide.

Drug therapy is one of the most commonly used treatments for CLBP, but side effects due to medication are inevitable.(Buchbinder et al., 2018; Clark & Horton, 2018) Considering that the condition of most patients with CLBP improves naturally regardless of treatment, nonpharmacologic and nonsurgical methods should be the first-line choice.(Qaseem et al., 2017; Wenger & Cifu, 2017) Clinical applications in patients with CLBP, physical therapy modalities (PTMs), such as transcutaneous electrical nerve stimulation (TENS) and far-infrared (FIR) irradiation therapy, is regard as a relatively safe, convenience and non-invasive option.(Khadilkar, Odebiyi, Brosseau, & Wells, 2008; Lai et al., 2014) Nowadays, exercise therapy is widely recommended as a valid way for pain relief and functional improvements by most clinical guidelines.(Bernstein et al., 2017; Chou et al., 2017; National Guideline, 2016; Qaseem et al., 2017) Among the numerous exercise therapies, therapeutic aquatic exercise (TAE) is often prescribed by clinical doctors and is becoming increasingly popular for alleviating pain and facilitating function.(Baena-Beato, Arroyo-Morales, Delgado-Fernandez, Gatto-Cardia, & Artero, 2013; Lahart & Metsios, 2018)

TAE refers to water-based treatments or exercise. With various properties, including its buoyancy pressure, density, thermal capacity, and conductivity,(Lahart & Metsios, 2018) water is an ideal environment to conduct an exercise program. TAE reduces the stress on intervertebral disk and intervertebral joint with the help of hydrostatic buoyancy; enables a large range of movement by supporting the body weight; improves lumbar muscle tone via its natural resistance; offers gentle manipulation on back because of turbulence and wave propagation; adjusts the velocity of exercise by changing the depth of water; moreover, dynamic water environment improves microcirculation, enhances balance and coordination, facilitates relaxation, and decreases the contracture.(Baena-Beato et al., 2013; Bressel, Dolny, & Gibbons, 2011; Carroll, Volpe, Morris, Saunders, & Clifford, 2017; Dundar, Solak, Yigit, Evcik, & Kavuncu, 2009; Rivas Neira, Pasqual Marques, Pegito Perez, Fernandez Cervantes, & Vivas Costa, 2017)

Some studies have shown that TAE aquatic exercise can be a safe and effective treatment approach for CLBP.(Barker et al., 2016; Carroll et al., 2017; Nguyen et al., 2017; Shi et al., 2018) Whether combined with other therapies or used alone, TAE is both beneficial to pain reduction and functional improvement.(Cuesta-Vargas et al., 2012; Karagulle & Karagulle, 2015) Although the effect of aquatic therapy on patients with CLBP has been explored,(Cuesta-Vargas et al., 2012; Cuesta-Vargas, White, Gonzalez-Sanchez, & Kuisma, 2015) the duration of most previous studies was short and did not include a long follow-up period. Both as a kind of non-invasive treatment, there are no studies investigating whether TAE could produce more benefits than PTMs for people with CLBP. Therefore, we will perform a single-blind randomized controlled trial (RCT) with long follow-up to observe the effects of TAE on people with CLBP versus PTMs.

**Methods/Design**

**Research goals and hypotheses**

We will design an RCT to conclude TAE and PTMs for people with low back pain to see:

Goal 1: whether TAE compared favorably with PTM for people with CLBP;

hypotheses for Aim 1: Patients in TAE group will receive more benefits in pain relieve and functional improvement than subjects in the PTMs group. There will be significant differences between two groups.

Goal 2: whether TAE yields long-term effects.

hypotheses for Aim 2: TAE will create a long-term effect on people with CLBP while PTMs will not. There will be significant differences between two groups during the fellow-up period.

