**Study design**

This study is a 3-month single-blind RCT with a 12-month follow-up (Trial registration: ChiCTR1800016396). All included participants will be randomly allocated into either the TAE group or the PTMs group. The interventions of two groups will be carried out in Shangti indoor constant temperature swimming pool and Shanghai Shangti Orthopeadics Hospital respectively. Experienced physiotherapists will carry out the measurements at baseline, after the 3-month intervention, at 6-month follow-up, and at 12-month follow-up from the beginning to determine whether short-term effects and long-term impacts will be achieved.

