**Randomization and blinding**

Randomization in a 1:1 ratio will be performed according to a computer-generated scheme, and participants will be assigned into the control group (PTMs) or the experimental group (TAE). A researcher who carries out the randomization with sealed and opaque envelopes will remain separated from the intervention team.

A group of assessors will be responsible for each block of the measurement, but they are not aware of the group assignments and remain distant from the invention. The instructors are masked to the study’s hypothesis and experimental purpose. To be ignorant of grouping when receiving a behavior-related treatment at the mean time is impossible for participants.

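### The Aim 2 hypothesis says PTMs have no long-term effect; this design cannot show that, and it can show a long-term effect of TAE only relative to PTMs

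*Protocol*

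**What the plan says.** In the Protocol, section Research goals and hypotheses, the second goal names no comparator: "Goal 2: whether TAE yields long-term effects". Its hypothesis has two sentences. The first makes a separate statement about each treatment: "TAE will create a long-term effect on people with CLBP while PTMs will not". The second is comparative: "There will be significant differences between two groups during the fellow-up period". Goal 1, just above, is worded throughout as TAE against PTMs, so the absolute wording is peculiar to Aim 2. Study design is similarly loose where it gives the purpose of the visits as finding out whether short- and long-term effects are achieved.

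The design is a two-arm comparison of active treatments: "All included participants will be randomly allocated into either the TAE group or the PTMs group", in a 1:1 ratio. Outcomes are measured at baseline and at 3, 6 and 12 months. The Statistical analysis section compares the arms by an adjusted group × time repeated measures ANOVA and by chi-square tests between groups. It specifies no within-arm test and no margin for absence of effect.

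On the natural course, the Introduction says that "the condition of most patients with CLBP improves naturally regardless of treatment", and also: "Approximately 33% of people experience relapse within 1 year after recovery".

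**The concern.** The first sentence of the hypothesis asserts that one treatment has a lasting effect and the other has none. Each assertion is about a treatment on its own, so each needs a reference for what would have happened without it. The trial has no such reference, and the protocol itself expects patients to improve whatever they receive. Selection for pain at entry (worst NRS of at least 3) may add regression to the mean.

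What is at stake is the conclusion. Suppose TAE is ahead of PTMs at 12 months. Judged against the hypothesis as worded, that result would be read as showing that PTMs, a treatment in clinical use, have no lasting benefit. It would show only that TAE did better.

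**Working it through.** No figure in the protocol is attached to Aim 2, so the main check is one of identification.

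**1. What the two arms can identify.** Let N be the mean improvement by 12 months from natural course and regression to the mean, T the effect of TAE against no treatment, and P the effect of PTMs against no treatment. Assume these add. Randomisation makes N the same in both arms on average.

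- Expected improvement under TAE: N + T
- Expected improvement under PTMs: N + P
- Difference: (N + T) − (N + P) = T − P

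There are two observable means and three unknowns. Only T − P is identified. The first sentence of the hypothesis claims T > 0 and P = 0; the second claims T − P ≠ 0.

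**2. A numerical example (hypothetical values).** Suppose RMDQ improves by 2.0 points under TAE and by 2.0 − 0.74 = 1.26 under PTMs. The difference of 0.74 is the one used in the sample size section (6.11 − 5.37). All three rows below fit these data exactly.

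| N | T | P | First sentence true? |
|---|---|---|---|
| 1.26 | 0.74 | 0 | yes |
| 0 | 2.0 | 1.26 | no: PTMs also last |
| 2.0 | 0 | −0.74 | no: TAE has no effect, PTMs harm |

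The third row requires PTMs to be harmful. If that is ruled out (P ≥ 0), then T ≥ T − P, so a TAE advantage does imply T > 0. Nothing comparable rescues P = 0.

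**3. Inputs for an illustration of size** (Sample size calculation). RMDQ SDs are 1.82 and 2.36, the means 5.37 and 6.11, the correlation 0.5, with 50 per arm and 20% missing.

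- Pooled SD = √((1.82² + 2.36²)/2) = 2.107
- 0.74 / 2.107 = 0.351, which reproduces the stated effect size of 0.35
- SD of change = 2.107 × √(2 × (1 − 0.5)) = 2.107
- Completers per arm = 50 × 0.8 = 40

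**4. Natural change alone, judged within an arm.** The protocol gives no size for natural improvement, so a range is assumed. The table gives the probability that a two-sided 5% paired t test in one arm is significant.

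| Assumed natural fall in RMDQ | 40 per arm | 50 per arm |
|---|---|---|
| 0.5 | 31% | 38% |
| 0.74 | 58% | 68% |
| 1.0 | 83% | 91% |
| 2.0 | >99.9% | >99.9% |

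A significant fall under TAE would therefore be weak evidence of an effect of TAE.

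**5. A null result under PTMs.** The 95% half-width for the mean change in one arm is t × 2.107/√n: about 0.60 points at n = 50 and 0.67 at n = 40. A non-significant change leaves values of that order open, and no margin says what would count as no effect.

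**6. The contrast that is identified.** The 95% half-width for the between-arm difference at one visit is t × 2.107 × √(2/n): about 0.84 points with 50 per arm and 0.94 with 40.

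**The case against.** The strongest reply is that the working hypothesis is the second sentence, "There will be significant differences between two groups during the fellow-up period". Randomisation, the 6- and 12-month visits and the group × time analysis can test it, and natural course affects both arms alike and cancels. The protocol's conclusion also frames the question as whether TAE does better than PTMs. All of this stands. A reader might therefore go too far in saying that the design can show neither half of the first sentence. The documents do not support that: a lasting TAE advantage would show a long-term effect of TAE relative to PTMs, and one against no treatment too if PTMs are assumed not to be harmful.

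A reader might also infer a false-confirmation rate from the pattern of a significant change under TAE and a non-significant one under PTMs. With the same true change in both arms that pattern has probability p(1 − p), where p is the within-arm power. At 40 per arm this is 0.489 × 0.511 = 25% for 0.66 points, 0.833 × 0.167 = 14% for 1.0 point and 0.992 × 0.008 = 0.8% for 1.5 points. The first value sits almost at the maximum of p(1 − p), and the pattern becomes rare as natural improvement grows. More importantly, the Statistical analysis section plans no within-arm test and no such rule, so none of these is an error rate of the planned analysis.

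What the reply does not do is repair the first sentence. The two sentences are not equivalent: the second can be true while PTMs also have a lasting effect.

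**Conclusion.** The point holds in a limited form. The claim that PTMs have no long-term effect cannot be established by this trial, even by a significant between-group difference at follow-up. The claim for TAE can be supported only relative to PTMs, or against no treatment under the added assumption that PTMs do no harm. The comparative part of Aim 2 is sound and its planned analysis fits it.

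No sample size, visit or test is affected. The effect is on what may be concluded. The identification argument rests on the two-arm design and the protocol's own statement on natural improvement. The within-arm percentages are illustrations only: they assume a size of natural change and a within-arm test that the protocol does not give, and they borrow SDs from the 3-month follow-up of another trial, of aquatic exercise against back school.

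**What to change.** Reword Goal 2 as a comparison, for example: whether any advantage of TAE over PTMs is present at the 6- and 12-month follow-ups. Reword its hypothesis to match: outcomes will be better with TAE than with PTMs at those visits. Delete the clause denying PTMs a long-term effect. Add one sentence saying that within-group changes are descriptive and will not be used to conclude that either treatment does or does not have a long-term effect. Bring the purpose of the visits in Study design into line.

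The change need not restrict Aim 2 to RMDQ or rank the two time points; those are separate choices. It needs no new patients, data or analysis. The price is a more modest claim: the trial will speak to TAE against PTMs, and not to either treatment against nothing.

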**Study design**

This study is a 3-month single-blind RCT with a 12-month follow-up (Trial registration: ChiCTR1800016396). All included participants will be randomly allocated into either the TAE group or the PTMs group. The interventions of two groups will be carried out in Shangti indoor constant temperature swimming pool and Shanghai Shangti Orthopeadics Hospital respectively. Experienced physiotherapists will carry out the measurements at baseline, after the 3-month intervention, at 6-month follow-up, and at 12-month follow-up from the beginning to determine whether short-term effects and long-term impacts will be achieved.

**Participant selection**

Subjects who meet all the inclusion criteria and do not have any of the exclusion criteria will be eligible for enrollment. Before undergoing other tests, participants will be examined via a questionnaire with the following entries: basic information (e.g., age, sex, height and weight), physical activity, medical history, medical expenditure, back pain duration, back pain intensity (at present, over the last week, the worst pain, and the average pain), and self-rated back disability.

**Inclusion criteria are as follows:**

1. Aged ranged from 18 to 65; 2. Pain, muscle tension or stiffness between the buttock band and the rib arch; may also have lower limb pain; 3. Pain intensity (when the most painful) ≥ 3 on the numeric rating scale (NRS); 4. CLBP lasting at least 3 months; 5. Voluntary participation in the trial and with written informed consent; 6. Accepted randomization. Subjects will be included if they meet all criteria above.

**Exclusion criteria are as follows:**

1. mental illness or cognitive impairment (Mini-mental State Examination, <24); 2. Specific lumbago, such as fracture, spinal stenosis, tumour infection and spinal structural abnormalities; 3. Lumbar dysfunction or pain caused by other diseases; 4. Complex back problems, such as spinal surgery; 5. Patients with severe and unstable cardiovascular, renal or liver diseases; 6. Received a regular low back pain exercise intervention during the past 6 months; 7. Pregnant or lactating; 8. Chlorine allergy; 9. Water-related anxiety or unable to adapt to an aquatic environment; 10. Urinary or faecalis incontinence; 11. Contagious skin diseases, ulcers or open wounds; 12. Medications that alter sensory perception. Subjects will be excluded if they have any of these criteria.

**Withdrawal criteria**

1. Patients lose interest; 2. Patients’ schedule conflict with the experimental arrangement; 3. Patients develop serious conditions, such as stroke; 4. Patients experience a side effect due to TAE or PTMs.

**Ethical considerations**

Before the measurement will implemented, informed consent will be signed by all participants interested in the study. The project is ratified by the ethics committee of the Shanghai University of Sport (number 2018042), Shanghai, China.

**Randomization and blinding**

Randomization in a 1:1 ratio will be performed according to a computer-generated scheme, and participants will be assigned into the control group (PTMs) or the experimental group (TAE). A researcher who carries out the randomization with sealed and opaque envelopes will remain separated from the intervention team.

A group of assessors will be responsible for each block of the measurement, but they are not aware of the group assignments and remain distant from the invention. The instructors are masked to the study’s hypothesis and experimental purpose. To be ignorant of grouping when receiving a behavior-related treatment at the mean time is impossible for participants.

**Interventions**

The intervention sessions will be carried out by a group of qualified physicotherapists who will not take part in the data collection. Both programs will last 12 weeks and will be administered twice per week for a total of 24 treatment sessions. The participants will be encouraged to complete the intervention as designed, and the adherence rate is expected to be at least 75%. Attendance frequency, medication changes, and adverse events during the sessions and after treatment will be filled out in a daily record form. Once a participant absents from the intervention sessions, he or she will be contacted immediately to determine the reason. Participants who withdraw halfway, fail to attend the evaluations, or miss more than 2 weeks will be regarded as drop-outs (Li et al., 2012).

**TAE group**

The temperature will be customized at 30 °C of water and 27.5 °C of environment to elicit the same heart response both in water and in air. The entire intervention will be completed in a swimming pool with a dimension of 20 m × 6 m and a depth of 1.3–1.5 m. To ensure that all of the participants will be submerged at their xiphoid bone level, some aquatic steps will be placed underwater as auxiliary forces.

The TAE protocol will be designed by the researcher in accordance with available scientific evidence. During the exercise, the participants will receive verbal, tactile, and visual information to correct their movements and ensure that the lumbar spine remains in a neutral position while standing. Thus, excessive loading on the spine will be avoided, and trunk muscles will be activated. The target exercise intensity will depend on the subject’s self-rated score of Rating of Perceived Exertion of approximately 13 in accordance with 60%–80% of maximum heart rate.(Wallace, Slattery, & Coutts, 2009)

The participants will start the exercise with an active warm-up for 10min to enhance neuromuscular activation. In the succeeding 40 min, they will perform an aquatic session, including abdominal bracing, vertical downward press, lateral downward press, slant downward press, straight leg raising, treading water, and deep water running. Finally, the participants will have a cool-down period for 10min. Table 1 shows the full description of the protocol.

All subjects will participate in the exercise in a group of 8–9 people. Weeks 1 and 2 are the learning period for subjects to become familiar with the actions. Then, the intensity of movements will be adjusted by changing the kickboard sizes. Thus, the neuromuscular stimulation will be maximized, and the subjects’ interest will also be maintained.

**PTMs group**

The subjects in the control group received TENS and IR irradiation therapy. Both modalities were focused on pain points, and each had a duration of 30 min.

TENS (model KD-2A, Beijing Yiyang Kangda Medical Instrument Co., Ltd., China) sends a bidirectional asymmetrical square wave at a frequency of 2 Hz to 160 Hz and a pulse width of 20 µs to 500 µs. The participants received TENS at a current frequency of 120 Hz and a pulse width of 100 µs. Disposable surface electrodes with dimensions of 50 mm × 50 mm were placed on the pain point, and pulse intensity was adjusted to produce a comfortable tingling sensation.(A, DO, L, & GA, 2008; Elserty, Kattabei, & Elhafez, 2016)

The IR apparatus (model LY-607A Foshan Lingyuan Medical Technology Co., Ltd., China) was placed with its lamp located 50 cm to 75 cm above the exposed area. The lamp direction was adjusted to ensure that radiation struck the surface at or near a right angle such that maximum penetration was achieved.(Diab & Moustafa, 2012; Gale, Rothbart, & Li, 2006) At 3–5 min after the instrument was energised, the patient was asked whether their sense of warmth was appropriate, and the lamp height was adjusted to prevent scalding.

**Outcome measures**

Clinical outcomes are classified as primary outcomes and secondary outcomes.

**Primary outcomes**

Disability was assessed with the Roland Morris Disability Questionnaire (RMDQ), which contains 24 items that are closely related to the daily life activities of patients with CLBP.(Mbada et al., 2017) The scores are as follows: 1 for checking ‘YES’ and 0 for checking ‘NO’. The final score varies from 0 to 24. Higher scores are associated with more severe disability.(Yi et al., 2012)

**Secondary outcomes**

1. Pain intensity was measured with the NRS, which consisted of 11 numbers from 0 to 10. The scores are set as follows: 0 as painless, 1–3 as mild pain, 4–6 as moderate pain and 7–10 as strong and unbearable pain. The subjects reported the pain intensity they feel at the present and that they experienced last week (slightest, average and most serious).(Morone, Rollman, Moore, Li, & Weiner, 2009)

2. Quality of life was measured with the Short-form (36) Health Survey (SF-36). SF-36 consists of eight scales, and a high score indicates low disability. The SF-36 questionnaire is reliable and relatively stable considering that its overall Cronbach’s α coefficient = 0.791 and r = 0.778.(Zhang, Qu, Lun, Guo, & Liu, 2012)

3. Anxiety state was measured with the self-rating anxiety scale (SAS). SAS is a 20-item self-reported assessment device.(Samakouri et al., 2012) Each question is based on the following responses: ‘rarely’, ‘sometimes’, ‘usually’ and ‘most of the time.’ A respondent should choose the appropriate statement on the basis of his condition within the past 1 or 2 weeks. The total raw score may vary from 20 to 80, a high score indicates high anxiety levels.(Samakouri et al., 2012)

4. Depression state was measured with the Zung Self-Rating Depression Scale (SDS). The SDS is a 20-item self-reported questionnaire covering affective, psychological and somatic symptoms associated with depression. Each item is scored on a Likert scale that ranges from 1 to 4. Total scores range from 20 to 80, wherein 20–44 is normal, 45–59 is mildly depressed, 60–69 is moderately depressed and >70 is severely depressed.

5. Sleep quality was measured with the Pittsburgh Sleep Quality Index (PSQI). The PSQI is a self-reported scale that is used to assess sleep quality over a 1-month period. The PSQI consists of 19 individual items and comprises 7 components that are used evaluate sleep quality from several different aspects, such as sleep latency, sleep duration, habitual sleep efficiency, sleep disturbances, sleeping medication use and daytime dysfunction. The global score of PSQI ranges from 0 to 21, wherein high values indicate poor sleep quality.(Hita-Contreras et al., 2014)

6. The Pain Anxiety Symptoms Scale (PASS) was used to evaluate pain-induced avoidance, fear, cognitive anxiety and physiological anxiety. The PASS contains 20 items. Each item is divided into 6 grades: ‘never’, ‘occasionally’, ‘sometimes’, ‘often’, ‘almost always’ and ‘always’. The total score ranges from 0 to 100. High scores are indicative of severe pain and anxiety symptoms. The internal consistency of the scale is good with Cronbach α = 0.92 and test–retest reliability intraclass correlation coefficient (ICC) = 0.90.(XY et al., 2017)

7. Kinaesiophobia was measured with the Tampa Scale for Kinaesiophobia (TSK). The 17-item version of the TSK is used to assess the fear of activity or (re)injury resulting from pain.(Aguiar, Bataglion, Visscher, Bevilaqua Grossi, & Chaves, 2017) It is rated by using a 4-point Likert scale that varies from ‘strongly disagree’ to ‘strongly agree’. The total score of this scale varies from 17 to 68, wherein a high score reflects high levels of kinaesthetic phobia.(Aguiar et al., 2017) The TSK has been confirmed to have acceptable reliability (ICC = 0.86) and excellent validity (Cronbach’s α = 0.74).(Wei et al., 2015)

8. The Fear Avoidance Beliefs Questionnaire (FABQ) was used to evaluate fear avoidance belief. The FABQ consists of 16 items, including 2 subscales that are used to evaluate the effects of fear avoidance beliefs on physical activity (items 1–5) and work (items 6–16). Each item is scored from 0 to 6. These scores correspond to strongly disagree, very disagree, disagree, uncertainty, agree, very agree and strongly agree. The total score of this scale ranges from 0 to 96. High scores indicate strong fear avoidance belief.

9. Minimal clinically important difference (MCID) was used to determine whether the treatment produces a significant clinical improvement in pain (NRS) and function (RMDQ). The definition of MCID is ‘the smallest difference or change in a clinical outcome that is perceived as beneficial to patient’s medical management, assuming no excessive side effects and costs’.(Fishbain, Gao, Lewis, & Zhang, 2016) MCID is an evidence-based assessment tool for behavioural interventions across an entire procedure.(Grant, Pedersen, Osilla, Kulesza, & D'Amico, 2016; Lee et al., 2017) A reduction of 2 or more in the NRS indicates positive clinical change.(Ostelo et al., 2008) And several studies have recommended that the MCID for RMDQ-24 is the absolute cut-off of 5 points.(Lee et al., 2017; Ostelo et al., 2008)

10. The participants’ overall assessment of the treatment was measured on the basis of the global perceived effect (GPE). The GPE scale requires patients to rate how much they have improved or deteriorated since they received the treatment. The use of this scale is widely advocated in pain research because it is easy and quick to understand and score, and its results are important to patients.(Evans, Bronfort, Maiers, Schulz, & Hartvigsen, 2014) The most meaningful changes can be observed in patients answering the scale at a predefined time point. The GPE scale has excellent reproducibility (ICC = 0.90–0.99), and its correlation with disability (r = 0.40–0.74) is strong.(Kamper et al., 2010)

11. Adverse events were collected from participants’ daily record forms. All pain (LBP or other pain) related to intervention or unrelated to intervention occurring during the research duration was considered.

12. The participants’ recommendation levels on the intervention that they received were classified as highly recommended, recommend, unclear, not recommended and strongly deprecated.

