**Statistical analysis**

Data will be collected and analyzed via SPSS 20.0 and Microsoft 2016. Considering that someone may drop out midway, all outcomes should be conducted by intention-to-treat analysis and per-protocol analysis. For baseline variables, we will detect the categorical variables (e.g. gender, education levels and occupation) with chi-square test and analyze the continuous variables (e.g. age, height, weight, BMI, and pain intensity) with independent t-test or Mann–Whitney U test to compare the statistical significance between the TAE group and the PTMs group. The results of descriptive statistics will be presented as mean ± standard deviation.

The experimental results were compared through adjusted two-way repeated measures ANOVA (group × time). The adjustment factors included gender, age, BMI, physical activity, LBP duration, NRS of the most severe LBP, medication, and smoking history. A chi-square test was conducted to compare the proportion of participants in each group who met the MCID for pain and function at postintervention. Although the MCID for RMDQ and NRS remains controversial, values of 5.0 and 2.0 are considered reasonable and commonly used. The χ2 test was also applied to determine the difference between the 2 groups for the proportion of participants reporting GPE, adverse events and treatment recommendations. The effect sizes were presented to measure the strength of any outcome indicators, where 0.2 ≤ Cohen’s d < 0.5 means a ‘small’ effect size, 0.5 ≤ Cohen’s d < 0.8 indicates a ‘medium’ effect size and Cohen’s d ≥ 0.8 reflects a ‘large’ effect size.

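### The adverse-event outcome counts any low back pain, related or not, in a chronic low back pain trial, and tests the undivided proportion, so disease dilutes any difference in intervention harm

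*Protocol*

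**What the plan says.** Item 11 under Secondary outcomes has two sentences. The first gives the source: "Adverse events were collected from participants’ daily record forms". The second gives the only content stated for the outcome: "All pain (LBP or other pain) related to intervention or unrelated to intervention occurring during the research duration was considered". It sets no threshold for worsening, and it mentions relatedness only to say that both kinds count.

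The Interventions section describes the form more broadly: "Attendance frequency, medication changes, and adverse events during the sessions and after treatment will be filled out in a daily record form". Table 3 marks adverse events at 3, 6 and 12 months.

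The Statistical analysis section applies a chi-square test to "the difference between the 2 groups for the proportion of participants reporting GPE, adverse events and treatment recommendations". It does not split events by type or relatedness.

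The inclusion criteria require "CLBP lasting at least 3 months" and a worst NRS score of at least 3. Elsewhere, the PTMs section names a physical risk of the lamp ("the lamp height was adjusted to prevent scalding"), and the Withdrawal criteria list a side effect of either intervention as a reason to leave the trial.

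**The concern.** An adverse-event comparison should show whether one intervention harms more people than the other. Here the stated rule counts the symptom for which every participant was enrolled, over a year, whatever its cause. Two things follow.

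- **Dilution.** A participant who would report low back pain anyway is already counted, so an injury from the intervention adds nothing to that arm's proportion. The more background pain there is, the smaller the visible difference.
- **Direction.** The Protocol's first hypothesis is that aquatic exercise relieves pain better than the physical modalities. If so, fewer participants in that arm report pain, and the arm looks safer because it works. The safety result then partly repeats the NRS outcome and can offset a real excess of injuries.

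At stake is a report of similar, or better, safety that the data collected under this rule could not support.

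**Working it through.** **The plan's own figure.** There is none to reproduce. The Protocol gives no adverse-event rate and no power for this test; its sample size was set on the RMDQ.

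**Inputs from the Protocol.** Planned enrolment is 50 per arm and α is 0.05 (Sample size calculation). The stated 20% missing rate leaves 50 × 0.80 = 40 per arm. The Introduction gives about 33% relapse within one year after recovery. I use that as a cautious low value for background pain, since these participants have not recovered.

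**Assumptions.** Background pain occurs in a proportion b of both arms. One intervention causes harm in a further proportion h, independently of background pain. I take h = 20% and b from 1% (background pain not counted) to 95%.

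**Step 1: what the undivided proportion shows.** The arm rates are p₁ = b and p₂ = b + (1 − b)h, so the visible difference is (1 − b)h.

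**Step 2: power of the two-sided comparison of proportions.**

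Power = Φ[(p₂ − p₁ − 1.96·SE₀)/SE₁], where SE₀ = √(2p̄(1 − p̄)/n), SE₁ = √((p₁(1 − p₁) + p₂(1 − p₂))/n) and p̄ is the mean of p₁ and p₂.

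For b = 0.33 and n = 50: p₂ = 0.33 + 0.67 × 0.20 = 0.464, the difference is 0.134, SE₀ = 0.0979 and SE₁ = 0.0969. Power = Φ[(0.134 − 1.96 × 0.0979)/0.0969] = Φ(−0.60) = 0.28.

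| Background b | Arm rates | Power, 50 per arm | Power, 40 per arm |
|---|---|---|---|
| 1% | 1.0% vs 20.8% | 0.90 | 0.82 |
| 33% | 33.0% vs 46.4% | 0.28 | 0.23 |
| 80% | 80% vs 84% | 0.07 | 0.07 |
| 90% | 90% vs 92% | 0.05 | 0.05 |
| 95% | 95% vs 96% | 0.04 | 0.04 |

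Exact enumeration of the uncorrected chi-square test with 50 per arm gives 0.96, 0.28, 0.09, 0.06 and 0.05 in the same order, so the pattern does not depend on the approximation. At 80% and above, power is close to α: the test hardly responds to the harm.

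**Step 3: a smaller harm.** With h = 10% and 50 per arm, power is 0.55 at b = 1%, 0.10 at b = 33% and 0.04 at b = 90%.

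**Step 4: masking by efficacy.** Suppose background pain is reported by 80% of controls but 75% of the aquatic arm, because that treatment works, and that aquatic exercise harms 20%. The aquatic arm shows 1 − 0.25 × 0.80 = 80%. The two arms look identical despite a 20% harm in one of them.

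**The case against.** A reader might infer that adverse events are defined as pain only, so that scalds, skin reactions or falls go unrecorded and the test would see no difference at all. The Protocol does not support that. Item 11 contains no exclusion, its first sentence is general, and the Interventions section puts adverse events without restriction on the daily form. The second sentence can fairly be read as clarifying that pain counts too. On that reading non-pain harms are collected, but they are pooled with background pain in one proportion.

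Nor should the list of foreseen harms be stretched. The stroke entry ("Patients develop serious conditions, such as stroke") is an example of a condition that ends participation, not a stated harm of treatment, and chlorine allergy is an exclusion criterion. Scalding is the one specific risk clearly tied to an intervention.

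Three further objections have weight. The background and harm rates are assumed, and at 33% the proportion is far from a ceiling. It is also unclear whether the form, which is not shown, captures persisting pain or only new episodes. Recording events regardless of cause is not itself an error, and an analysis plan, not shown here, could tabulate by relatedness. Finally, the trial is not sized for rare harms: 5/50 versus 0/50 gives a two-sided Fisher p = 0.056, and for true rates of 10% versus 0% Fisher's test has power of about 0.38.

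What remains is the text itself. It counts pain of any cause, sets no worsening criterion, and tests one undivided proportion. Later tabulation can separate relatedness only if it was recorded, and the Protocol does not say that it will be.

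**Conclusion.** The point holds in this limited form. On either reading of item 11, background low back pain enters the adverse-event proportion, overlaps with the NRS outcome and dilutes intervention harm. Under the assumed model with 50 per arm, power for a 20% excess harm falls from about 0.90 to about 0.28 at a 33% background, and to 0.04–0.08 at 80–95%. These figures rest on assumed rates, independence of harm and background pain, and a form that captures ongoing pain. If it captures only new episodes, the lower backgrounds apply. The loss is already large at 33%, so the conclusion does not need a near-ceiling rate. It concerns one secondary outcome, but that outcome is the trial's safety comparison, and the correction is cheap.

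**What to change.** Reconcile Withdrawal criteria, Interventions, PTMs group, Secondary outcomes item 11 and Statistical analysis, so that they describe one adverse-event outcome:

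1. State that adverse events include non-pain events as well as pain.
2. Record type, seriousness and relatedness for each event on the existing daily form.
3. Compare participants with intervention-related events between arms, giving counts, a risk difference with confidence interval, and Fisher's exact test, since expected counts may be small.
4. Report low back pain not attributed to the intervention separately, outside that comparison.

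The cost is one definition, a few lines on the form and slightly more recording. Participants know their treatment, so relatedness will need judgement. Fisher's test keeps power of about 0.89 for 1.0% versus 20.8% with 50 per arm, but power for rarer harms stays limited, so the interval should carry the interpretation and a non-significant result should not be read as equal safety.
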